#### 4.3.2.4. Additional analyses

We will also conduct a thorough process evaluation that includes results from: (a) intervention fidelity indicators (section 2.3.2 and 5.1); and (b) exit interviews. Quantitative data will be reported using descriptive techniques; Qualitative data will be transcribed verbatim and personal identifiers removed. Transcripts will be analyzed with a thematic analysis approach using MAXQDA software. Coding will be inductive and will start with open-coding followed by further iterations to fit the data using the constant comparison method, until theoretical saturation is reached. Differences will be solved by reflective discussion within the study team. Once consensus is reached, a coding dictionary will be developed and the data recoded independently by two researchers. There will be two analysis levels: 1. individual and 2. cross-case analysis (i.e. grouped by age and site). In individual analysis we will triangulate patient and parent outcome and qualitative data with provider views to better understand whether and how processes were influenced (or influenced) the intervention. We will use cross case analyses to explore similarities and differences between cases and compare processes to explain differences in outcomes in relevant subgroups.

Finally, we will also conduct several exploratory analyses including: (a) Mediation analysis: We propose that the intervention effect on patient's HRQoL is mediated by parental activation (PA) (Figure 5). If we find a positive intervention effect on patient's HRQoL we will explore PA mediation (measured at 8 and 16 weeks) using the counterfactual framework. The PA mediated (indirect) effect will be computed through G-estimation incorporating confounders of the mediator-outcome association, e.g. time since diagnosis or parent S-TAI-Trait

score. A similar approach will be used to explore whether PA mediates intervention's effect on parent HRQoL. These exploratory analyses, albeit limited because of the small sample size, could shed light on PQ response's mechanisms and help further refine the intervention; (b) Age as an effect modifier: we will evaluate whether the effect of the intervention on mean PedsQL and PQ-MSAS total scores over 16-w is modified by age. (c) Subgroup analysis: if sample size permits, we will assess the effect of PQ-Response on symptom burden as reported by children 7-12 years old using the same analytical approach described for patient level outcomes; (d) Parent-patient reports relationship: we will explore correlation (Spearman), convergence and divergence between parent and patient (whenever available) HRQoL and symptom burden reports for total, subscale, and specific item scores.

### 4.3.3. Considerations regarding missing data

Effective data collection at scheduled times will be monitored and intermittent attrition will be minimized using the strategies described in section 2.3.2. PediQUEST web is designed to avoid involuntary non-completion of items, and incomplete surveys have been less than 1% in prior studies. For the purposes of scoring PedsQL and MSAS we will proceed as suggested by the authors of the scales by imputing the mean to the missing items if more than 50% of the scales have been completed. Exit interview information will inform type of missing data/drop-out process and missing data handling approach. For outcomes where missing completely at random is a plausible assumption, we will do complete case analysis. If missing at random (MR) is highly likely, we will use multiple imputation or inverse probability weighting, depending on the statistical model being considered. For not MR data we will use sensitivity analyses. In all cases we will assess robustness of the estimates to missing data assumptions.

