### 2.3.3. Rationale for intervention's "dose," frequency, and administration:

Weekly PQ-Surveys: Surveys will be administered weekly to capture distress in real time. A longer interval may make the intervention less relevant if surveys miss the distress event or participants answer about distress that occurred longer ago. Ideally, one would want participants to report distress on an "as needed" basis, however this approach is challenging from a design point of view as controls may have less incentive to report. For this reason, we decided to collect weekly measures in both arms. Weekly reporting allows the Response team to intervene and propose prevention strategies if symptoms are thought to be recurrent. During the pilot, adherence to weekly surveys was good; over 75% of participants answered 50% of weekly surveys or more, and 60% answered 75% of weekly surveys or more.

Response team intervention: Response teams will contact the families: (i) on a regular basis over the intervention period (we encourage at least monthly encounters), (ii) to attend to PQ reports, and (iii) to monitor treatment recommendations. Regular contacts are proposed as a means of standardizing the intervention across patients with varying experiences of distress.

Response teams will be informed of criteria for potential distress including:

- a. a PQ-MSAS total score of 3.2 or higher (for children using PQ-MSAS 7-12 (see section 2.5.1.) the equivalent threshold value is 9) or individual symptom scores of 50 or more, or
- b. PedsQL total score below 60.

A PQ-MSAS score of 3.2 (or 9) was chosen as a threshold because it is the minimum score that includes one severe symptom (i.e. that participant reported at least two of the following characteristics for a given symptom: it is very severe, or happens almost all the time, or bothers him/her a lot or very much). It could also represent a report with five mild or moderate symptoms, which also warrants evaluation. In addition, teams will be advised that any symptom score of 50 or more may indicate current or past distress. Similarly, the score of PedsQL of 60 denotes a poor quality of life (this represents approximately one standard deviation below the average PedsQL score in pediatric cancer populations). These threshold scores will promote optimal Response team intervention. Further, this approach helps standardize the response to distress and as such increases replicability of the intervention.

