## 2.6. Sample Size

The target sample size (SS) is N=136 participants 68 in each arm. Texas Children's Hospital will have a slightly lower accrual goal of 34 total dyads, as opposed to 50 dyads, since they will collect data for a shorter period of time. Based on prior work, we estimate that there will be approximately 32 eligible patients/site/year, representing a total of 288 eligible patients over the 36 months the study will be available for recruitment. Pilot data suggest an enrollment rate of 70% which translates into approximately 200 patient-parent dyads, our enrollment target. After the two-week run-in period, non-responders will be excluded. Assuming that about 25% will be non-responders, a conservative estimate based on pilot data, there would remain 150 patients to be randomized to either the intervention (n=75) or usual cancer care (control, n=75). Based on previous work we estimate an attrition of approximately 10%, mainly due to dropouts. We therefore expect to collect complete data on a minimum of 136 dyads, 68 per group, a sample size that achieves sufficient power for all outcomes.

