### 2.6.1. Power considerations

Although the SS is mainly driven by pragmatic considerations (target population is small), power calculations were conducted and indicate that our projected minimal SS of 68 children per group provide sufficient power for both primary and secondary outcomes for clinically meaningful effect sizes. All power calculations presented below were computed with two sample independent one-side tests,  $\alpha=0.05$  unless otherwise specified. For Aims 1 and 2 power estimates are conservative because they only use one observation per subject (average across time) without accounting for the repeated measures within subject.

*Aim 1 HRQoL (primary) and Symptom (secondary) outcomes:* Standard deviations for these outcomes were estimated using data from our PQ study (39 weeks follow up, surveys answered when attending clinic or once a month). For each child, we identified all 16-w periods with  $\geq 6$  surveys and calculated mean PedsQL total and mean PQ-MSAS total scores for each 16-w period. We randomly selected one period per child and estimated the standard deviation of 16-week PedsQL means (SD). Strategy was repeated 10 times and a pooled estimate was calculated. A sample size of 136 children (68 per group) achieves 85% power to detect a 4.4 point increase (MCID) in the mean over 16-w PedsQL Total score (SD for both groups 9.5), and a 95% power to detect a 3-point decrease in mean over 16-w PQ-MSAS total score (SD = 5.3). These power calculations are conservative as they are based on mixed responses coming from parents and children, while in the current proposal responses from different informants will be considered in separate analyses and are expected to have less variability.

*Aim 2 Parental anxiety (S-TAI-State), and depression (CES-D-10) (secondary outcomes):* A sample size of 68 parents per group achieves more than 80% power to detect a moderate to large effect size (Cohen's  $d = 0.43$ ). For example, this effect size would correspond to a difference of 5.2 points in mean S-TAI-State (SD=12.2).

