## 4.3. Statistical methods

### 4.3.1. Overview

All statistical analysis will be conducted on an intention-to-treat basis, i.e. all randomized participants with baseline and at least one post-baseline measurement will be analyzed by original treatment assignment, regardless of adherence. Baseline characteristics will be described and compared between groups using summary measures (e.g. means, medians, rates) and tests selected based on variable distribution. Analyses will be adjusted for factors used in the stratified randomization (center, age group and type of cancer). In addition, if, despite efforts to standardize intervention delivery (section 5.1), we identify substantial differences in fidelity across sites, we will evaluate effect modification by site including the site  $\times$  intervention interaction in the models. The False Discovery Rate criterion will be used to correct for multiple testing in non-planned analyses. Co-I [name] has been the primary biostatistician for all prior PQ analyses and is best suited to head the PQ Response's analysis, along with her team at Deakin University. The PI and Co-I [name] will be part of the leadership team. While all Co-Is will be involved in analysis and manuscript writing, some may take a more prominent role according to their specific expertise (e.g. [name], [name] with aim 2, and [name] with aim 3). DFCI will coordinate data cleaning and programming.

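### Section 4.3.3 allows complete-case analysis, informed by exit interviews held after follow-up, in conflict with the 4.3.1 analysis set and the 4.3.2.1 mixed model

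*Protocol*

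**What the plan says.** Section 4.3.3 first says how the missing-data method will be settled: "Exit interview information will inform type of missing data/drop-out process and missing data handling approach". It then gives three branches, chosen outcome by outcome:

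- MCAR plausible: "For outcomes where missing completely at random is a plausible assumption, we will do complete case analysis".
- MAR highly likely: multiple imputation or inverse probability weighting.
- Not MAR: sensitivity analyses.

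A robustness check is promised whichever branch is used. The section does not say which branch applies to the primary outcome, and it does not define a complete case.

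Section 4.3.1 sets the analysis population as "all randomized participants with baseline and at least one post-baseline measurement", analysed as randomised. Section 4.3.2.1 fits a mixed linear model with a patient random effect, categorical time, group, their interaction and the stratification factors. Section 4.3.2.2 carries the same approach over to the parent scores.

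Under section 2.5.3 the research coordinators hold the exit interviews, ideally within a week of the last survey, and the invitation goes out 12 weeks after a death where the child has died. Section 3.2 says research staff are unblinded after randomisation. On response, section 2.3.3 reports that in the pilot "over 75% of participants answered 50% of weekly surveys or more, and 60% answered 75% of weekly surveys or more".

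**The concern.** There are two difficulties.

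The first is timing. The interviews that inform the choice of method take place after a participant's outcome data are in, and the staff who hold them know the arm. With no rule for choosing a branch, the handling of the primary outcome can be settled after both outcomes and allocation are known. The primary endpoint is also to be analysed at months 12 and 24 (section 5.1.3), before all the exit interviews can be available.

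The second is the complete-case branch itself. It would remove participants whom section 4.3.1 says will be analysed. Nor is it the better choice under its own condition: if data are MCAR, the mixed model is also unbiased and uses every answered survey; if they are only MAR, the mixed model remains valid and complete-case analysis may not. MCAR is in any case doubtful for the weekly scores. Section 2.3.2 removes a dyad when either member misses four surveys in a row, and section 2.5.3 plans for deaths on study.

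At stake are precision and, where the best responders differ from the rest, the direction of the result.

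**Working it through.** **Inputs**

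- Section 2.6.1: 68 per arm, difference 4.4 points, "SD for both groups 9.5", alpha 0.05, "computed with two sample independent one-side tests".
- Section 2.6: "there would remain 150 patients to be randomized" (75 per arm), attrition about 10%, complete data expected on at least 136 dyads, run-in non-response about 25%.
- Section 1.2.1: weekly measurement for 16 weeks.
- Section 2.3.3: the pilot response figures quoted above.

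**1. The plan's own power**

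Power = Φ(δ / (σ√(2/n)) − 1.645), with n per arm.

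σ√(2/n) = 9.5 × √(2/68) = 1.629; 4.4 / 1.629 = 2.701; 2.701 − 1.645 = 1.056; Φ(1.056) = 85.4%.

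The noncentral t gives 85.1%. The stated 85% is reproduced.

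**2. Complete means retained to the end, as section 2.6 uses complete data**

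136 / 150 = 91% kept, 68 per arm, power 85% as planned. The other 150 − 136 = 14 dyads would be left out, although any of them with a baseline and one later survey belongs to the section 4.3.1 set.

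**3. Complete means all 16 weekly surveys: bound from the pilot**

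Anyone with a full series is among those who answered 75% or more. That was 60% of pilot participants, so at most 60% can be complete and at least 40% are lost.

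- Bound 60%: 0.60 × 150 = 90, or 45 per arm. 4.4 / (9.5 × √(2/45)) = 2.197; Φ(2.197 − 1.645) = 71%.
- If the run-in removed exactly the lowest quarter: 60 / 75 = 80%, so at least 20% are lost. 0.80 × 150 = 120, or 60 per arm, power 81%.

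These are best cases, since they treat everyone at or above 75% as fully complete.

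**4. Complete means all 16 weekly surveys: assumed response model**

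Assumption: each person's number of answered surveys out of 16 is beta-binomial, with P(at least 12) = 0.60. Because the pilot text says only that more than 75% answered half or more, P(at least 8) was varied from 0.75 to 0.90. The result was then conditioned on at least 2 of 3 run-in surveys answered. Figures are for one informant.

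| P(at least 8 of 16) | Passing run-in | All 16 answered, given run-in passed | Of 150 | One-sided power |
|---|---|---|---|---|
| 0.75 | 72% | 44% | 65 | 59% |
| 0.80 | 75% | 31% | 47 | 47% |
| 0.85 | 78% | 20% | 31 | 36% |
| 0.90 | 80% | 12% | 17 | 25% |

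The modelled share passing the run-in, 72% to 80%, is close to the 75% that section 2.6 assumes. Without conditioning on the run-in, the share complete runs from 32% down to 10%.

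**The case against.** The best defence is that the text is loose rather than wrong. Complete case is one of three branches, it is conditional on MCAR, and a robustness check always follows. The primary model and analysis set are fixed elsewhere. Sections 2.1 and 6.5 place the analysis with a separate statistical team, and branch criteria or the definition of a complete case may be in an analysis plan that is not shown. The protocol's own usage also points away from the all-16-surveys reading: section 2.6 expects complete data on 136 of 150 dyads, and section 2.6.1 estimated its SD from 16-week windows with as few as six surveys. For outcomes measured only at entry and week 16, complete-case analysis is an ordinary choice.

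Much of this stands, and it rules out several stronger readings:

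- A reader might infer that complete case is the default or the primary analysis. Section 4.3.3 does not say so.
- A reader might infer that only a small fraction of dyads would certainly be kept. That needs both the all-16-surveys definition and a response model that the documents do not give.
- A reader might multiply the loss by requiring both informants to be complete. Sections 1.3.2 and 2.6.1 analyse the informants separately, so no planned primary analysis needs that.
- A reader might infer that unblinded coordinators choose the method. The text says only that the interviews inform it.
- A reader might infer that imputation would create scores after a child's death. Section 4.3.3 does not mention death; it neither plans nor excludes this.

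The conflict remains after these concessions. The complete-case sentence is stated policy, not silence, and a robustness check does not settle which analysis is primary.

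**Conclusion.** The point holds in limited form. The complete-case branch contradicts the section 4.3.1 analysis set and, for the repeated weekly and monthly outcomes, is no better than the section 4.3.2.1 model under any condition in which the protocol would use it. Letting interviews held after follow-up inform the method in an unblinded trial, with no branch named for the primary outcome, leaves room for a choice made after the results are known.

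The size cannot be fixed from the protocol. It runs from no loss of power (retention meaning) to 25% to 59% one-sided power (all 16 surveys, one informant). The first figure rests on section 2.6's attrition assumption. The second rests on the beta-binomial model and on trial respondents behaving like pilot participants. The firmest statement under the all-16-surveys reading is the bound: at least 40% lost before run-in selection, or at least 20% if the run-in removed exactly the lowest quarter.

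That the mixed model uses all observed scores is inferred from sections 4.3.1 and 4.3.2.1 together; neither says it outright. Its validity under MAR also requires the mean and covariance structure to be adequate.

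**What to change.** Rewrite section 4.3.3 as follows:

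1. Delete the complete-case branch for the repeated-measures outcomes.
2. State that the primary analysis is the likelihood-based mixed model of section 4.3.2.1, fitted to all observed scores in the section 4.3.1 analysis set and valid under MAR.
3. Pre-specify the not-at-random sensitivity analyses before any unblinded results are seen, and state that no scores are imputed after death.
4. Limit exit interviews to interpretation and to the sensitivity analyses.

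The cost is one rewritten paragraph and a little extra analysis work. Recruitment, data collection and sample size are unaffected.

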## 5. Methods: Monitoring

### 5.1. Data Monitoring

#### 5.1.1. Formal committee

This is a small multisite clinical trial of a supportive care intervention with a risk profile that is comparable to usual cancer care. As such, data monitoring will be primarily carried out by the Study Data Center at DFCI, and a small Data and Safety Monitoring Board (DSMB). A 5-member DSMB composed of five co-investigators representing different disciplines and expertise will be established (see

| Table 4. Data and Safety Monitoring Board (DSMB)                                                                                   |                    |           |     |    |    |                         |
|------------------------------------------------------------------------------------------------------------------------------------|--------------------|-----------|-----|----|----|-------------------------|
| Member                                                                                                                             | Title/Discipline   | Expertise |     |    |    | Role                    |
|                                                                                                                                    |                    | PCR       | CTR | BR | QR |                         |
| [name]                                                                                                            | PhD, Biostatistics | X         | X   |    |    | Study Lead Statistician |
| [name]                                                                                                               | DNsC, Nursing      | X         | X   |    | X  | Independent Monitor     |
| [name]                                                                                                                 | PhD, Nursing       | X         | X   |    |    | Independent Monitor     |
| [name]                                                                                                            | PhD, Psychology    | X         |     | X  | X  | Independent Monitor     |
| [name]                                                                                                             | MD, MPH, Medicine  | X         | X   |    | X  | Co-investigator         |
| References: PCR: Palliative care Research; CTR: Clinical trials research; BR: Behavioral research; QR: Qualitative research |                    |           |     |    |    |                         |

table 4). Three members do not participate in the study (MB, MC, CG) and will act as Independent Monitors. The committee will be convened at the beginning of the study via conference calls, to provide input and

guidance on study evaluation, including quality assurance and safety issues, as well as data management activities and interim analysis stopping rules.

The DSMB will be in charge of monitoring: 1) data quality for completeness, timeliness, and accuracy including conformance with informed consent requirements; 2) participants' accrual and retention; 3) adverse events; 4) participants' withdrawals, compliance issues or any complaints about the research; 5) intervention fidelity indicators; 6) compliance with data management procedures; 7) reviewing any protocol modifications/deviations that may occur between DSMB review periods; and, 8) reviewing interim analysis and making recommendations if appropriate. All data reviewed by the DSMB will be blinded (except for interim analysis results as explained in 5.1.3). DSMB virtual meetings will take place at least quarterly by videoconference calls. DSMB members will provide quarterly input and feedback to the Steering Committee, via e-mail and conference calls.

### 5.1.2. Reports

During the 36-month data collection period, the SDC will generate a number of reports to monitor data quality and trial progress. Specifically, the SDC will produce:

- Weekly data monitoring reports informing about the recruitment process (number of participants screened, identified as eligible, and enrolled),
- Monthly reports assessing data quality (completeness, missing and inconsistent data), follow-up (participants' response rate, number of dropouts and reasons), and process measures (to determine whether the intervention is being delivered as expected, e.g. number of participants who did not have the initial meeting with the Response team within three weeks of randomization and other intervention fidelity indicators (see section 2.3.2)).
- An annual report summarizing recruitment progress, data quality, protocol violation, and adverse events will be produced to be sent to the local IRBs.

Reports will present figures for the entire study and stratified by site.

